### **8.4 Subjects Trial duration**

The estimated trial duration for each participant is approximately 8 weeks from first contact, including a 15 Day (+  $\leq 4$  Days) treatment duration and a 2-week post-treatment follow-up visit.

[figure not shown]

## **8.5 Trial Objectives**

### **8.5.1 Primary Objective**

- To determine if the addition of Megestrol Acetate increases the anti-proliferative effect of Letrozole when given for 15 days pre-operatively in patients with early-stage, ER-positive breast cancer, as measured by change in Ki67.

### **8.5.2 Secondary Objectives**

- To compare and correlate the biological effects of Letrozole alone compared to Letrozole plus Megestrol Acetate using other immunohistochemical markers of tumour response: Caspase 3, Aurora kinase A, change in expression of the androgen and progesterone receptors, and the absolute value of Ki67 at Day 15
- To compare and correlate the change in Ki67 and the biological effects of low dose Megestrol Acetate compared to high dose Megestrol Acetate using other immunohistochemical markers of tumour response: Caspase 3, Aurora kinase A, change in expression of the androgen and progesterone receptors, and the absolute value of Ki67 at Day 15
- To assess the safety and tolerability of the combination of Letrozole +/- Megestrol Acetate by recording and assessing adverse and serious adverse events.

### **8.5.3 Exploratory objectives**

- To assess progestin-induced ER reprogramming following treatment with Letrozole and Megestrol Acetate, using transcription factor mapping (ChIP-seq) of ER, and RNA sequencing (Addenbrooke's patients only).
- To compare and correlate the biological effects of Letrozole alone compared to Letrozole plus Megestrol Acetate and also the effects of low dose Megestrol Acetate compared to high dose Megestrol Acetate using epithelial mesenchymal transition markers.
- To correlate efficacy and exploratory findings of this trial with breast cancer genomic profiling datasets [22].

Optional Imaging sub-study (Addenbrooke's patients only): to noninvasively assess the anti-proliferative effect of Letrozole vs. Letrozole + Megestrol Acetate using F-FLT-PET/MRI imaging indices, and to correlate this with the changes observed in Ki67. (Please see Appendix 4 F-FLT PET/MR Imaging Sub-Study for further details).

## **8.6 Trial Endpoints**

### **8.6.1 Primary Endpoint**

Change in tumour proliferation measured by Ki67 immuno-histochemical (IHC) assessment (%) between baseline and day 15 (+/-4 Days).

### **8.6.2 Secondary endpoints:**

#### **Biological Endpoints**

- Change in tumour apoptosis between baseline and Day 15 (+/-4 Days), measured by Caspase 3 (IHC)
- Change in expression of androgen receptor and PR (IHC) between baseline and Day 15 (+/-4 Days)
- Change in proliferation by Aurora Kinase A (IHC) between baseline and Day 15 (+/-4 Days)
- Absolute value of Ki67 at Day 15 (+/-4 Days)

[figure not shown]**Safety Endpoints**

- Incidence of Serious Adverse Events (SAEs)
- Incidence of Adverse Events (AEs) of all grades (CTCAE Version 4.03)

**8.6.3 Exploratory Endpoints**

Other translational research questions will be addressed:

- Transcription factor mapping (ChIP-seq) of ER
- Gene expression changes associated with treatment, measured by RNA-sequencing
- Change in epithelial mesenchymal transition markers (IHC) between baseline and Day 15 (+ $\leq 4$  Days)
- Correlate differences in response to treatments with breast cancer genomic profiling datasets
- Changes in tumour proliferation measured by  $^{18}\text{F}$ FLT-PET/MRI (optional imaging sub-study only) and correlate these changes with changes observed in Ki67.

**9 Selection and withdrawal of subjects****9.1 Inclusion Criteria**

To be included in the trial the patient must satisfy all of the following:

- Histologically confirmed breast adenocarcinoma
- Postmenopausal women, defined as having experienced at least one of the following:
  - 12 months of natural (spontaneous) amenorrhea with an appropriate clinical profile (e.g.  $\geq 50$  years, history of vasomotor symptoms) or
  - six months of spontaneous amenorrhea with serum FSH and oestradiol levels consistent with postmenopause or
  - surgical bilateral oophorectomy (with or without hysterectomy) at least six weeks ago.
- Core biopsy confirmation of invasive carcinoma on core biopsy,  $\geq \text{T1c}$ , either clinical NX or N0-N3
- ER positive (Allred $\geq 3$ ) and HER2 negative
- 2 groups of patients are potentially eligible:
  - Cohort A: Patients whose cancers have been deemed to be operable by the Multi-Disciplinary Team (MDT) with tumour excision planned for the next 2-6 weeks
  - Cohort B: Patients with early or locoregionally advanced breast cancer planned for primary endocrine therapy either in lieu of tumour excision or as neoadjuvant therapy before tumour excision – such patients must begin PIONEER trial therapy prior to starting any other endocrine therapy.
- ECOG performance status of 0, 1 or 2
- Adequate Liver, Renal and Bone marrow function, defined as:
  - Adequate liver function where bilirubin is  $\leq 1.5 \times \text{ULN}$
  - Adequate renal function with a serum creatinine  $\leq 1.5 \times \text{ULN}$
  - Adequate bone marrow function with ANC  $\geq 1.0 \times 10^9/\text{L}$  and Platelet count  $\geq 100 \times 10^9/\text{L}$
- Written informed consent (IC) to participate in the trial and to donation of tissue

[figure not shown]

## **9.2 Exclusion Criteria**

The presence of any of the following will preclude patient inclusion:

- History of hormone replacement therapy in the last 6 months
- Previous treatment with tamoxifen or an aromatase inhibitor in the last 6 months
- Known hypersensitivity or contraindications to Aromatase Inhibitors (AIs) or Megestrol acetate
- Known allergy to lactose
- Known to have a progestogen-containing intrauterine system in situ, unless removed prior to randomisation
- Known metastatic disease on presentation
- Recurrent breast cancer (patients with a new primary invasive breast cancer will be eligible to participate)
- Serious concomitant disorders that would compromise the safety of the patient or compromise the patient's ability to complete the trial, at the discretion of the investigator
- Treatment with an investigational drug within 4 weeks before randomisation
- Inability to swallow orally administered medication and patients with gastrointestinal disorders likely to interfere with absorption of the trial medication
- Inability to give informed consent (IC)

## **9.3 Treatment Assignment and Randomisation Number**

Eligible patients will be randomly assigned, using a minimization method with a random element, to either the control arm (Letrozole alone) or one of the two research arms (Letrozole with Megestrol Acetate at low and high dose) in a 1:1.5:1.5 ratio.

The stratification factors are:

- tumour grade (1,2,3),
- ductal vs. lobular subtype,
- intensity of ER staining (3-6, 7-8), reported on the initial diagnostic core biopsy, to ensure that each arm of the trial is well balanced.

Randomisation must be complete prior to the start of trial treatment.

Randomisation will be implemented using a web-based central randomisation system by the relevant participating site staff. The web-based central randomisation system will allocate patient treatment arm and trial numbers sequentially in the order in which the patients are randomised.

At the site initiation, the trial coordinator will train site staff in how to access and use the randomisation system.

This is an open-label trial. The histopathologist assessing the biological response (primary endpoint, Ki67 expression by IHC; secondary endpoint, Caspase-3 by IHC) will, however, be blinded as to treatment allocation.

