### 10.1.2 Subject Registration/Randomisation

Registration and randomisation must be complete prior to the start of trial treatment. Patients will be registered following confirmation of eligibility (including results of screening assessments). Local site staff will complete the 'patient details', 'informed consent' (CRF not original consent form) and 'eligibility' CRFs and forward them to the central coordinating office to register the patient and provide authorisation to randomise. Appropriate staff at the local site will then randomise the patient upon confirmation of central approval. Data will be entered into a web-based central randomisation system (Sealed Envelope) by the relevant local site staff. The web-based central randomisation system will allocate patient trial numbers sequentially in the order in which the patients are randomised.

Supporting documentation required for patient randomisation will include results of an initial diagnostic core biopsy, specifically delineating ER status, histological subtype (ductal or lobular) and tumour grade, in addition to the patient details, IC and eligibility forms. These must be medically reviewed to confirm randomisation. Any queries must be resolved prior to randomisation. The PI or co-investigator will sign the eligibility CRF to confirm eligibility.

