### **14.2 Number of Subjects to be enrolled**

In this open-label, three-arm, randomized, phase II trial; patients will be randomised in a ratio 1(A):1.5(B):1.5(C) in favour of the 2 combination arms of Letrozole + Megestrol acetate. Our hypothesis is that the addition of Megestrol acetate increases the anti-proliferative effect of Letrozole when given for 2 weeks pre-operatively in patients with early-stage, ER-positive breast cancer, as measured by Ki-67.

Based on the results from the *Opportune* study [23], where a significantly greater geometric mean Ki-67 suppression of 83.8% (one-sided 95% CI,  $\geq$  79.0%) was reported for the combination arm, and 66.0% (95% CI,  $\leq$ 75.4%) for anastrozole alone

[figure not shown]

arm (geometric mean ratio [combination: anastrozole], 0.48; 95% CI,  $\leq 0.72$ ;  $P = .004$ ), this translates to the estimated standard deviation is 0.242. We therefore have assumed a mean 66% reduction in Ki67 for the Letrozole alone arm of PIONEER (Arm A). It is anticipated that there is a mean 77.5% reduction in Ki67 in arms B and C for all patients (approximately one third PR negative, and two thirds PR positive), and a mean 80.0% reduction in Ki67 in arms B and C for patients with PR positive, which was based on the anti-proliferative effect seen in preclinical models [5]. Enrichment design is applied with the overall significance level of 5% (one-sided) ( $5\% (\alpha) = 2.5\% (\alpha_{all}) + 2.5\% (\alpha_{PR+})$ ) and a power of 80%, and common standard deviation of 0.242, using the two-sample t-test comparing Arm A vs. Arm (B+C):

- all patients

a total of 189 patients (Arm A  $n=47$ , Arm B  $n=71$ , Arm C  $n=71$ ) is needed to detect the mean reduction in Ki67 of 66% in Arm A to 77.5% in Arm (B+C);

- patients with PR positive breast cancer

a total of 149 PR positive patients (Arm A  $n=37$ , Arm B  $n=56$ , Arm C  $n=56$ ) is needed to detect the mean reduction in Ki67 of 66% in Arm A to 80.0% in Arm (B+C);

The total number of evaluable patients required is 189 with 149 PR positive. It is anticipated that this will require approximately 10% more patients to be randomised, to account for patients that may not be evaluable.

It is therefore planned to randomise approximately 210 patients with 166 PR positive ( $210 \times 90\% = 189$ ,  $166 \times 90\% = 149$ ).

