The comparison of Ki67 reduction between Arm A and Arm (B+C) will be performed for all patients; if  $p_{all} \leq 0.025$ , it can be concluded that the addition of Megestrol acetate increases the anti-proliferative effect of Letrozole for all patients.

If there is no evidence of Ki67 reduction for all patients, the comparison of Ki67 reduction between Arm A and Arm (B+C) will be performed in patients with PR positive only; if  $p_{PR+} \leq 0.025$ , it can be concluded that the addition of Megestrol acetate increases the anti-proliferative effect of Letrozole for patients with PR positive.

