### **14.3 Enriched data monitoring**

The patient population will be monitored (PR positive vs. PR negative) regularly during patient recruitment in order to achieve the required sample size for patients with PR positive. This will be regularly reviewed by the Independent Data Monitoring Committee (IDMC) and the recruitment plan will be amended accordingly if needed.

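### PR status defines the second primary test but is not a minimisation factor, so the PR-positive split between arms is left to chance; this is a cheap improvement, not an error of validity

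*Protocol*

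**What the plan says.** Section 9.3 allocates 1:1.5:1.5 by minimisation with a random element. Its factors are grade, ductal or lobular subtype, and "intensity of ER staining (3-6, 7-8), reported on the initial diagnostic core biopsy, to ensure that each arm of the trial is well balanced". The synopsis, section 5 and section 11.1 give the same three factors. Section 10.1.2 requires the diagnostic biopsy report before randomisation, "specifically delineating ER status, histological subtype (ductal or lobular) and tumour grade"; PR is not named.

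Section 14.2 divides the one-sided 5% into 2.5% for all patients and 2.5% for PR-positive patients. It sets a separate sample size for "patients with PR positive breast cancer": 149, split 37/56/56. If the all-patient test fails, the comparison of Arm A with Arms B and C pooled "will be performed in patients with PR positive only", and p ≤ 0.025 there supports a conclusion for that group.

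The control that the protocol places on PR is in section 14.3: "The patient population will be monitored (PR positive vs. PR negative) regularly during patient recruitment". Its purpose is to reach the PR-positive total. It says nothing about the division of PR-positive patients between arms.

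**The concern.** Minimisation is meant to balance the variables that matter most to the analysis. Here PR status carries half the alpha and defines a primary analysis population. Section 14.2 also expects it to modify the effect: 80.0% reduction with the combination in PR-positive patients, against 77.5% overall. It is nevertheless absent from the allocation scheme.

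Two things are at stake. The first is the size of the PR-positive control group, the smallest cell in either primary comparison (37 planned), which may drift from plan. The second is a chance difference in PR mix between Arm A and Arms B+C, which could shift the all-patient result if PR status is related to Ki67 change. The t-test named in section 14.1 does not adjust for that.

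**Working it through.** **Inputs (section 14.2).** 189 evaluable patients, 47 in Arm A and 142 in B+C. SD 0.242, one-sided alpha 0.025, 80% power. Mean reduction 66% against 77.5% (all patients) or 80.0% (PR positive). PR-positive total: 149 as planned, or two thirds of 189 = 126 as the same section describes the mix.

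**1. Reproduce the plan's figures.** With B+C three times the size of Arm A, n_A = (1 + 1/3)(1.960 + 0.842)² × 0.242² / δ².
- All patients, δ = 0.115: n_A = 46.3, rounded up to 47, total 188. The plan states 189, so this reproduces; noncentral-t power at 47 against 142 is 80.2%.
- PR positive, δ = 0.14: n_A = 31.3, rounded up to 32, total 128. The plan states 149, which has 85.8% power at 37 against 112. That mismatch, and the conflict between 149/189 = 79% and the stated two thirds, are separate points. Both totals are carried below.

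**2. Chance split of PR-positive patients.** If allocation ignores PR, the number in Arm A is hypergeometric, with mean 47 × M/189 and variance 47 × (M/189) × (1 − M/189) × (142/188).
- M = 149: mean 37.1, variance 5.92, SD 2.43, 95% range 32 to 42.
- M = 126: mean 31.3, variance 7.89, SD 2.81, 95% range 26 to 37.

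**3. Power of the PR-positive test (66% against 80%, noncentral t).**

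| PR-positive total | Lower end (A / B+C) | Near the mean | Upper end | Average over chance splits |
|---|---|---|---|---|
| 149 | 32/117: 82.1% | 37/112: 85.8% | 42/107: 88.4% | 85.7% |
| 126 | 26/100: 74.1% | 31/95: 79.3% | 37/89: 83.5% | 79.3% |

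Fixing the split therefore gains about 0.1 point of power on average, or nothing. What it removes is the spread.

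**4. Validity.** In 20,000 simulated trials under the null with PR left out of the allocation, the PR-positive test rejected in 2.5% of trials. With a PR effect on outcome of 0.1 in every arm, it rejected in 2.4%.

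**5. Difference in PR mix.** The SD of the difference in PR-positive share is SD × (1/47 + 1/142).
- M = 149: 2.43 × 0.0283 = 0.069, so ±13.5 percentage points (95%). At the extremes of step 2 the shares are 68% in A against 82% in B+C, or 89% against 75%.
- M = 126: 2.81 × 0.0283 = 0.080, so ±15.6 points.

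**6. Effect on the all-patient comparison.** Section 14.2 uses 66% in Arm A both overall and in PR-positive patients, so it assumes no PR effect in the control arm. In B+C, 77.5% overall and 80.0% in the PR-positive two thirds imply (77.5 − 2/3 × 80.0)/(1/3) = 72.5% in PR-negative patients, a gap of 7.5 points.
- On those assumptions only the B+C share matters. Its 95% range is ±1.96 × 2.43/142 = ±3.4 points (±3.9 for M = 126). This moves the B+C mean by 0.034 × 7.5 = 0.25 point (0.29).
- If the same 7.5-point gap also held in Arm A, which the plan does not assume, the full imbalance would count: 0.135 × 7.5 = 1.0 point (0.156 × 7.5 = 1.2).
- For scale, the target is 11.5 points and the standard error is 24.2 × √(1/47 + 1/142) = 4.1 points.

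**The case against.** The strongest reply is that nothing here is wrong. Section 9.3 claims balance only on the factors it lists, and those lists agree throughout the protocol. A randomised comparison within a baseline subgroup is valid without stratifying on that subgroup. Chance raises the Arm A count about as often as it lowers it. Power depends mainly on the PR-positive total, which section 14.3 does monitor. ER score is minimised, and section 7.1 says that ER induces PR expression, so some indirect balance is plausible. Baseline tissue is taken before treatment, so treatment cannot alter baseline PR status.

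All of this stands, and it rules out the stronger readings that a reader might infer: that the PR-positive test is biased or invalid, that its power is systematically eroded, or that PR imbalance materially distorts the all-patient result. Steps 3, 4 and 6 support none of these. Nor does the silence of section 10.1.2 show that PR is unknown at randomisation; that list matches the factors in use.

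What the reply does not remove is the uncontrolled split itself. Indirect balance through ER score is not enforced, and monitoring the total does not govern the division between arms. The choice of minimisation factors is fixed in the protocol and cannot be supplied by a later analysis plan.

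**Conclusion.** The omission is real and its consequences are modest. PR status defines a primary test with a planned count in each arm, and nothing in the protocol holds those counts near plan. Against an expected 37 PR-positive patients in Arm A, the plausible range is 32 to 42 when 149 are PR positive, and power stays above 80% throughout. If only the stated two thirds are PR positive, the range is 26 to 37, and an unlucky split could take power to about 74%. The lower average in that case (79.3% against 85.7%) comes from the smaller PR-positive total, not from imbalance. The all-patient comparison shifts by about 0.3 point on the protocol's assumptions, and by about 1 point if the PR gap also held in the control arm.

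The ranges assume simple random allocation with evaluable arms fixed at 47 and 142. They are likely an upper bound, because ER score may correlate with PR.

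**What to change.** Add PR status (positive or negative on the diagnostic core biopsy) as a fourth minimisation factor in section 9.3, and make the same change in the synopsis, section 5 and section 11.1. Add PR to the biopsy results required in section 10.1.2, so that membership of the PR-positive population is on record before open-label allocation. Where patients are already allocated, adjust the all-patient comparison for baseline PR status.

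The cost is one more two-level factor in the minimisation, one more field in the web randomisation system, and the amendment that goes with it. PR is already tracked during recruitment, so no new test is needed, and the sample size does not change.

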**For patients in Cohort A (pre-operative patients)**

Patients will undergo breast cancer tumour excision (e.g. Lumpectomy or mastectomy +/- lymph node dissection) as determined by the local MDT, in accordance with both local protocols and the patient's consent. Tumour excision should be performed 15 days (+ ≤4 days) from the start of the trial treatment. Trial treatment should be continued until tumour excision or biopsy.

The biopsy should be taken during breast tumour excision provided this is performed on Day 15 (+ ≤4 days). If for logistical reasons, it is not possible to take the biopsy during the tumour excision OR if the patient does not have breast tumour excision scheduled on Day 15 (+ ≤4 days), then the patient will be asked to undergo a core biopsy on Day 15 (+ ≤4 days) to assess the effect of the trial treatment and can continue treatment with Letrozole alone (regardless of randomised arm) until tumour excision. These patients will continue with the study schedule and complete the study two weeks after their rescheduled date of tumour excision at the end of trial visit.

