**Patients in Cohort B of the trial**  
**(primary endocrine therapy - either instead of tumour excision or as neoadjuvant therapy before tumour excision-)**

Patients will be asked to undergo a core biopsy on Day 15 (+ ≤4 days) to assess the effect of the trial treatment. Subsequently they will start standard of care (i.e. off-trial) endocrine therapy after the "Day 15" research biopsy. This standard of care endocrine therapy will be determined by their treating physician.

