### **11.2 Maximum duration of treatment of a patient**

Treatment in all three arms should be continued until tumour excision and/or core biopsy on day 15 (+ ≤4 days) unless there is evidence of unacceptable toxicity, progression or the patient requests to discontinue. Treatment can be planned for 13-14 days if exceptional circumstances mean that tumour excision or Day 15 biopsy can not be scheduled on Day 15 (+ ≤4 days).

In exceptional circumstances where tumour excision is delayed beyond the planned 15 day treatment period, we allow treatment to be continued for up to an additional 4 days.

Should patients experience significant AEs that could potentially impact on the operability, Megestrol acetate should be discontinued permanently whereas Letrozole should be continued until breast tumour excision is performed. If breast tumour excision cannot be performed on day 15 (+ ≤4 days) patients will be required to undergo an additional core biopsy on day 15 (+ ≤4 days) to assess the effect of the trial treatment.

[figure not shown]

Following the 19 days of study treatment, in the event of surgical delay beyond this time, patients may choose to continue treatment with Letrozole alone until the day of tumour excision.

Patients will be excluded from the final analysis if they do not complete at least 13 of the full 15 day pre-operative window dosing schedule, necessitating recruitment of an additional patient.

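### Cohort (A or B) is known before randomisation, but it is neither a minimisation factor nor a covariate in the fixed primary t-test, which also leaves out the three factors that are minimised on

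*Protocol*

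**What the plan says.** **Two cohorts.** Section 9.1 of the protocol (also the synopsis and Section 5) admits two groups. Cohort A has operable disease with excision planned within 2 to 6 weeks. Cohort B has early or locoregionally advanced disease planned for primary endocrine therapy. Membership is part of eligibility. Section 5 also requires the excision date to be booked before randomisation for patients who are planned for excision.

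**Day 15 tissue.** For Cohort A, Section 10.3.3 says: "The biopsy should be taken during breast tumour excision provided this is performed on Day 15", within the allowed window. It provides a separate core biopsy when excision is not scheduled in the window or sampling at surgery is not possible. For Cohort B it says: "Patients will be asked to undergo a core biopsy on Day 15", again with the window. Section 13.1.1 scores biopsy and post-surgical material by one method.

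**Randomisation.** Section 9.3 specifies minimisation with a random element on three factors: grade, ductal versus lobular subtype, and ER intensity, "reported on the initial diagnostic core biopsy, to ensure that each arm of the trial is well balanced". The synopsis, Section 5 and Section 11.1 name the same three. Section 14.2 states that "patients will be randomised in a ratio 1(A):1.5(B):1.5(C) in favour of the 2 combination arms".

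**Primary analysis.** Section 14.1 fixes a standard t-test of Arm A against Arms B and C combined in evaluable patients. Section 14.2 sizes the trial on a two-sample t-test "and a power of 80%, and common standard deviation of 0.242". Neither section mentions a covariate.

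**The concern.** Cohort separates patients with different treatment plans and, in part, different disease extent. It also goes with the setting in which the second Ki67 measurement is obtained. Either could plausibly relate to the size of the Ki67 fall. The protocol balances on three baseline features to keep the arms comparable, yet leaves out one that is equally available at randomisation.

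The fixed test then uses none of this baseline information. Two things follow. First, if Cohort B happens to be over-represented in one arm, the unadjusted difference absorbs part of any cohort difference. With 1:3 allocation and 47 patients in Arm A, such imbalances are not rare. Second, whatever variation in Ki67 change is explained by cohort, grade, subtype or ER intensity remains in the error term, although the data to remove it are already collected.

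**Working it through.** **1. Reproduce the design.** Inputs from Section 14.2: difference 0.775 − 0.66 = 0.115; SD 0.242; one-sided 2.5%; power 80%; ratio 1:3 for Arm A against Arms B and C combined; stated evaluable numbers 47 and 71 + 71 = 142, total 189.

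- Arm A size = (1 + 1/3) × [0.242 × (1.960 + 0.842) / 0.115]² = 46.3, rounded up to 47. The total is 4 × 47 = 188, in agreement with 189.
- Standard error at 47 against 142 = 0.242 × √(1/47 + 1/142) = 0.242 × 0.1683 = 0.0407.
- Power = 80.2% by noncentral t (80.6% by the normal approximation).

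**2. Assumptions.** The protocol gives neither the Cohort B share, *f*, nor the cohort difference in mean Ki67 reduction, *d*. I take *f* = 10% to 30% and *d* = 0.05 to 0.15.

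**3. Chance imbalance without balancing on cohort.** SD of the difference in Cohort B share between Arm A and the combined arms = √[f(1 − f)(1/47 + 1/142)]. The 95% limit is 1.96 times this.

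- f = 10%: SD 0.050, limit 9.9 percentage points
- f = 20%: SD 0.067, limit 13.2 points
- f = 30%: SD 0.077, limit 15.1 points

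This treats cohort as unrelated to the three minimisation factors. If they are related, minimisation already reduces the imbalance somewhat.

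**4. Shift in the unadjusted estimate at that limit.** Shift = 1.96 × SD × d.

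- Smallest: 0.099 × 0.05 = 0.005, and 0.005 / 0.115 = 4% of the planned effect
- Middle (f = 20%, d = 0.10): 0.132 × 0.10 = 0.013, or 11%
- Largest: 0.151 × 0.15 = 0.023, or 20%

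**5. Precision gained by adjusting for cohort.** Residual SD = √[0.242² − f(1 − f)d²]; power by noncentral t with 189 − 3 = 186 degrees of freedom.

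- f = 10%, d = 0.05: √(0.058564 − 0.000225) = 0.2415, power 80.4%
- f = 20%, d = 0.10: √(0.058564 − 0.001600) = 0.2387, power 81.3%
- f = 30%, d = 0.15: √(0.058564 − 0.004725) = 0.2320, power 83.4%

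The further gain from grade, subtype and ER intensity cannot be computed, because the protocol does not say how strongly they predict Ki67 change.

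**The case against.** **The test is valid as it stands.** Averaged over randomisations, the unadjusted t-test is unbiased and leaving cohort out does not inflate its type I error. Chance imbalance exists for every baseline variable that is not balanced on. This is correct, and it limits the point to efficiency and to robustness in the one randomisation that will be realised.

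**The size is assumed.** Both inputs are mine. The shift quoted is at the 95% limit, and a one-SD imbalance gives about half of it. Some of any cohort difference may run through grade, subtype or ER intensity, which are already balanced. The SD of 0.242 comes from a pre-operative window study and may contain no between-cohort variance. In that case the power of the unadjusted test would start below 80.2%, and adjustment would bring it back towards that figure. All of this stands, and it is why the result is given as a range.

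**The statistical analysis plan may deal with it.** Section 14.1 promises one, and it may add adjusted or sensitivity analyses. But the minimisation factors belong to the protocol, and the protocol itself names the primary test.

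**Stronger readings that the documents do not support.** A reader might infer that Cohort A compares a core with resected tissue while Cohort B compares a core with a core. Sections 10.3.2, 10.3.3, 13.1.1 and 16 describe Cohort A's Day 15 sample mainly as a biopsy taken during excision or as needle passes from the surgical specimen. Some Cohort A patients have a separate core biopsy instead. Cohort therefore largely fixes the setting and does not strictly fix the specimen type.

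A reader might also take Section 11.2 ("Should patients experience significant AEs that could potentially impact on the operability") to show that tissue source follows treatment arm. The text says only that megestrol acetate stops and letrozole continues until excision. A separate sentence covers any excision that cannot be done in the window. The link is an inference with no frequency attached, and patients who fall short of the dosing minimum are not evaluable in any case.

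**Conclusion.** The point holds as a modest improvement that costs nothing in patients. It is not an error that invalidates the primary test. Cohort is available before randomisation, is not balanced on, and is not adjusted for; nor are the three factors that the trial chose to balance.

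The cost is exposure to chance imbalance and some lost precision. Under the stated assumptions the gain in power is between 0.2 and 3.2 percentage points. At the lower end both effects are negligible. They become noticeable only if the cohorts differ in mean Ki67 reduction by about 10 points or more, which the documents neither show nor exclude. There is no basis for calling the comparison systematically biased.

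**What to change.** - In Sections 14.1 and 14.2, replace the t-test with a linear model for Ki67 change. Compare Arm A with Arms B and C combined, adjusted for grade, subtype, ER intensity and cohort. Use the same model in the PR-positive comparison, and keep both one-sided 2.5% levels. The model spends 7 parameters (intercept, arm, two for grade, and one each for subtype, ER intensity and cohort), which leaves 189 − 7 = 182 degrees of freedom.
- If recruitment still allows, add cohort to the minimisation factors in Section 9.3. If not, the covariate alone does most of the work.
- Record the source of the Day 15 tissue (taken at excision, or separate core biopsy) and report it descriptively by arm. Do not restrict an analysis to patients by tissue source: it is settled after randomisation, so the restriction could break the comparability of the arms.

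**Cost:** an amendment to the analysis text, one more field on the randomisation form if minimisation is changed, and one recorded item per Day 15 sample. The sample size of 189 evaluable patients is unchanged. The model should be fixed before any outcome data are examined by arm.
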